### Participants and eligibility criteria

#### Criteria for CYWS facilities

Inclusion criteria for CYWS facilities are (1) responsible for a number of UYRs of whom at least 8 UYRs have declared an interest in participation; (2) willing to participate in training and implementation of screenings and documentation; (3) agree to name a mental health coordinator (MHC) from their staff; (4) in the case of randomization to BETTER CARE, willing to implement “Mein Weg”; (5) agree to send a caregiver to participate in TF-CBT; and (6) availability of at least one eligible therapist for 10 UYRs ≤ 1 h travel time.

#### Criteria for participants

Inclusion criteria for participants are (1) age 12–20 years; (2) arrived in Germany as unaccompanied minors; (3) applied for asylum or intend to do so; (4) being cared for by a CYWS facility at screening; (5) written informed consent given by participant and legal guardian (if < 16 years at screening); and (6) reported at least one traumatic event in line with the DSM-5 A criterion. No exclusion criteria have been defined for participants in the RCT.

If they are to be referred to and treated with TF-CBT in the event of randomization to BETTER CARE, UYRs have to meet the following criteria: (1) a score (self-report) of ≥ 25 points in the initial screening with the Child and Adolescent Trauma Screen, second version (CATS-2) [26]; and (2) diagnosis of PTSD (according to International Classification of Diseases 10 [ICD-10]) or any mental disorder (ICD-10) as confirmed by the therapist. Exclusion criteria for TF-CBT treatment are (1) acute danger to themselves or others; (2) acute psychosis; (3) acute suicidality; (4) severe substance abuse; or (5) severe mental disability (each as judged by the therapist). Study participants who were excluded from the study will be referred to a more appropriate treatment for their needs, such as inpatient mental health care institutions.

#### Criteria for therapists

Therapists need to meet the following inclusion criteria to participate: (1) licensed as either child and adolescent psychotherapist or psychological psychotherapist or child and adolescent psychiatrist; (2) willingness to participate (i.e., motivation to learn TF-CBT and to invest additional time into training and documentation); (3) written informed consent; and (4) willingness to treat up to 3 UYRs with PTSD. There are no exclusion criteria.

### Sample size

The sample size calculation was based on a two-step procedure due to the hierarchical data structure. First, we calculated the sample size for an individual randomized study based on our previous data. We assumed a small effect size (ES) of *d* = 0.2 for “Mein Weg” as this intervention is implemented with a non-clinical sample and a medium ES of *d* = 0.5 for TF-CBT. The latter ES reflects the fact that our previous trial with *d* = 1.08 (CATS [19]) was uncontrolled, and treatment was provided in a university setting with highly experienced therapists. We plan to compare BETTER CARE with usual care+ and expect a small effect (*d* ≥ 0.30) in favor of BETTER CARE at 12 months (T2) on the CATS-2. A power analysis for a t-test with independent samples (α = 0.05, two-tailed, power 0.80) results in a minimum sample size of 2 × 176 participants (352 in total). The second step will factor in the cluster structure of the data with participants nested within CYWS facilities/therapists clusters. We assume that each CYWS facility will recruit on average *n* = 10 participants. The design effect is needed for the inflation of the group sample size: DE = 1 + (*m* − 1) × ICC with the fixed cluster size *m* and the intra-cluster correlation coefficient ICC. For the fixed cluster size, a value of *m* = 8 was set because of an estimated dropout rate of 20% of participants (UYRs). For the ICC, a liberal value of 0.05 was assumed to control for the correlation of the outcome of participants living in the same facility. In this context, the DE is 1 + (8–1) × 0.05 = 1.35 which results in a group size of 352 × 1.35 = 476 participants. As every facility recruits 10 participants on average, 48 facilities are needed for the whole trial. With an assumed dropout rate of 10% of facilities, an oversampling of 6 facilities is needed, resulting in 54 facilities (= 2 × 27 facilities). Thus, the overall participant sample within these facilities is estimated as 54 × 10 = 540 participants.

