### Statistical analysis

We will analyze the primary outcome (CATS-2 severity score) using hierarchical linear mixed (HLM) models to account for the nesting of cases within clusters. Mixed effect models, with fixed effects of group (BETTER CARE vs usual care+) and time (intake (T0) versus 6 months (T1) versus 12 months (T2)) as well as their interaction, will be conducted. Primary outcome analysis will be based on the ITT sample (*N* = 540 participants) as the mixed model approach will take missing data and different numbers of reassessments per participant/patient into account. A significance level of *α* = 0.05 will be used. We will also use exploratory mixed linear models to examine the impact of other variables (gender, age, nationality, asylum status) on our primary outcome. Separate (hierarchical) linear mixed models will be used to analyze the secondary outcomes.

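### The 20% participant dropout lowers the design effect but never raises the sample, so 54 facilities give about 72% power for d = 0.30 after the plan's own losses, not 80%

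*Protocol article*

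**What the plan says.** All figures are in the Sample size section of the protocol article.

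- The planning comparison is an unadjusted two-sample t-test: "A power analysis for a t-test with independent samples (α = 0.05, two-tailed, power 0.80". The effect is d = 0.30 "in favor of BETTER CARE at 12 months (T2) on the CATS-2", and the calculation "results in a minimum sample size of 2 × 176 participants (352 in total".
- Each facility is assumed to recruit 10 participants on average. The cluster size in the design effect is set lower, at 8, "because of an estimated dropout rate of 20% of participants (UYRs". With an ICC of 0.05 this gives a design effect of 1.35 and 476 participants.
- The 476 is then turned into facilities: "As every facility recruits 10 participants on average, 48 facilities are needed for the whole trial".
- Ten per cent of facilities are expected to drop out, so 48 becomes 54 (27 per arm), and 54 × 10 gives 540 participants.

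The Statistical analysis section adds: "Primary outcome analysis will be based on the ITT sample", with N = 540, and relies on the mixed model to deal with missing data.

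**The concern.** The calculation uses two cluster sizes. It uses 8 (retained) in the design effect, where the smaller number reduces the requirement. It uses 10 (recruited) when converting participants to facilities, where the larger number reduces it. Expected participant dropout thus makes the trial smaller; it should make it larger. Facility dropout is a separate loss and is allowed for.

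The stated 80% power for the primary comparison rests on this chain. If the chain fails, a null result would carry more weight against BETTER CARE than the design justifies. There is also little slack, since the Strengths and limitations section already warns that falling numbers of young refugees could make recruitment harder.

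**Working it through.** **Inputs**, all from the Sample size section: two-sided α = 0.05, power 0.80, d = 0.30 (SD = 1), 10 recruited per facility, 20% participant dropout, ICC = 0.05, 10% facility dropout, equal arms.

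**1. The plan's own figures reproduce.**
- A two-sample t-test with 176 per arm has 80.1% power, so 352 in total.
- Design effect: 1 + (8 − 1) × 0.05 = 1.35.
- 352 × 1.35 = 475.2, rounded up to 476.
- 476 / 10 = 47.6, so 48 facilities. 48 / 0.9 = 53.3, so 54. 54 × 10 = 540.

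**2. What the 476 counts.** The t-test needs 352 independent 12-month values. A design effect computed with m = 8 describes clusters that contribute 8 values each. So 476 participants must have a 12-month value, at 8 per facility, and the divisor should be 8.

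**3. What the planned sample delivers.** With K facilities contributing m values each, in equal arms:

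SE = √(2 × DE / (K × m / 2)), and power ≈ Φ(0.30/SE − 1.96).

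For K = 48 and m = 8, 384 participants are analysed:
- Effective N = 384 / 1.35 = 284, against 352 needed.
- SE = √(2 × 1.35 / 192) = 0.1186.
- 0.30 / 0.1186 = 2.53, so power = Φ(0.57) = 71.6%.
- Noncentral t with K − 2 = 46 degrees of freedom: 69.7%.
- Detectable d at 80% power: 2.80 × 0.1186 = 0.33.

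| Facilities at 12 months | Values per facility | Analysed | DE | Power, normal | Power, t with K − 2 df |
|---|---|---|---|---|---|
| 48 (both planned losses) | 8 | 384 | 1.35 | 71.6% | 69.7% |
| 54 (no facility lost) | 8 | 432 | 1.35 | 76.5% | 75.0% |
| 48 (no participant lost) | 10 | 480 | 1.45 | 77.9% | 76.2% |
| 54 (nothing lost) | 10 | 540 | 1.45 | 82.5% | 81.1% |

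Only the last row reaches 80%, and it requires that neither of the plan's two dropout rates occurs.

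**4. Could either cluster size, used throughout, give 48?**
- With 8: 475.2 / 8 = 59.4, so 60 retained facilities. 60 / 0.9 = 66.7, so 67 enrolled, or 68 for equal arms (about 680 participants).
- With 10: 352 × 1.45 = 510.4, and 510.4 / 10 = 51.04, so 52 retained facilities.

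The figure of 48 arises only when the two are mixed.

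**5. What baseline adjustment could recover.** The article gives no correlation r between T0 and T2 CATS-2, so these values are assumptions. They also assume that adjustment leaves the design effect at 1.35. Adjustment multiplies the variance by 1 − r². With 384 analysed, the normal approximation gives 80% when 1 − r² = 384 / 475.2, so r = 0.44. With 46 degrees of freedom r must be about 0.47. At r = 0.30 power is 75.5% (normal); at r = 0.50 it is 83.2%. If the group-by-time term is instead tested as a plain T0-to-T2 change, the variance factor is 2(1 − r). Then r must be about 0.60, and r = 0.30 gives 57%.

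**The case against.** The strongest reply is that the t-test is only a planning device. The analysis actually planned is a mixed model using T0, T1 and T2 on all randomised participants, and it may well be more efficient. That is fair as far as it goes. Whether the planned model has 80% power is unknown, because no correlation is stated. But the section derives its 80% from an unadjusted comparison at 12 months and claims no gain from baseline. A likelihood-based model protects against some bias from missing data; it does not supply the missing 12-month values. Depending on how the group-by-time term is tested, the gain could even be a loss.

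Second, the 72% is conditional on losing 10% of facilities. If all 54 stay it is about 77%. This condition belongs in the statement of the problem, but it is the plan's own assumption, and the figure without it is still below 80%.

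Third, the ICC is itself uncertain. With 384 analysed, power ranges from about 81% at ICC 0.01 to about 62% at ICC 0.10 (normal approximation), a wider span than the shortfall at issue. This is true, but it cuts both ways and does not reconcile the two cluster sizes at the plan's chosen ICC.

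Finally, randomisation, the estimand and the type I error are untouched. The error lies in a stated figure and does not make the trial invalid.

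**Conclusion.** The sample-size calculation is wrong as written. At the plan's own effect size, ICC and two dropout rates, 54 enrolled facilities leave about 384 participants at 12 months. For the unadjusted comparison, power for d = 0.30 is about 72% (normal approximation), or 70% with facility-based degrees of freedom. The detectable effect at 80% power is d = 0.33. Without facility loss, power is about 77%. These figures assume equal arms, facilities of equal size and a standardised SD of 1. The conclusion concerns the support given for the 80%; it does not establish the power of the mixed model, which cannot be computed from the article.

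**What to change.** Correct the Sample size section so that one cluster size is used throughout, and restate the result: 54 facilities and 540 recruited participants are expected to yield about 384 analysed at 12 months, which is about 72% power for d = 0.30 or 80% power for d = 0.33 without adjustment.

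If the sponsor wants to keep the 80% claim at the current size, the section should say that the primary analysis adjusts for baseline CATS-2 and should state the assumed T0–T2 correlation with its source. That correlation must be at least about 0.44 (normal approximation) or 0.47 (46 degrees of freedom).

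Either correction costs only rewording, plus a less favourable stated power in the first case, and neither needs extra enrolment. The alternative, keeping 80% for the unadjusted comparison, would mean about 68 facilities and 680 participants, that is 14 facilities and 140 participants more than planned.

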### Procedure

Once a CYWS facility has declared its interest in participating in the study, MHCs will be informed about the study details, eligibility criteria, informed consent, and randomization procedure in an initial information workshop. They will also be informed about participant inclusion criteria to ensure that all the participants who are willing to participate are indeed eligible. Eligibility of a facility will be evaluated using a facility questionnaire which will be completed online in the context of a nationwide CYWS survey which is part of the study. Once all facility inclusion criteria are clear, the head of the facility and all principal investigators (RR, HK, RK, UZ) will sign a cooperation agreement.

Baseline screening (T0) will be undertaken at the respective CYWS facility by study staff and MHCs. All participants will complete self-report questionnaires on an iPad. Proxy-report questionnaires will be completed by the respective caregiver of a participant. After screening, the study center will communicate the result of the subsequent randomization to the facility by letter and telephone. In a next step, each participant will receive a short written report documenting the main findings from the screening to be shared with the caregiver. Follow-up assessments will take place for both study arms, 6 (T1) and 12 months (T2) after randomization (see Fig. 3 for all assessment details). It will also be followed by a short written report on the assessment results. A sub-sample of *n* = 100 participants will be followed up for two further assessments at 18 (T3) and 24 months (T4) after randomization. They will complete additional questionnaires on group climate, social support, and post-migration factors at each time point (T0–T4, see the “Measures” section).

**Fig. 3 Fig3:**
[figure not shown]
Schedule of enrollment, interventions, and assessments (SPIRIT Figure). AUDIT = Alcohol Use Disorder Identification Test; BAOS = Brief Acculturation Orientation Scale; BSAS = Brief Sociocultural Adaptation Scale; CAMHSRI-REF = Child and Adolescent Mental Health Service Receipt Inventory adapted for refugee youths; CATS-2 = Child and Adolescent Trauma Screen 2; CUDIT-R = Cannabis Use Disorder Identification Test, Revised; CYWS = Child and youth welfare service; DSSYR = Daily Stressors Scale for Young Refugees; GAD-7 = Generalized Anxiety Disorder 7; GCIC = Group Climate Instrument for Children; HoNOSCA = Health of the Nation Outcome Scales for Children and Adolescents; PHQ-9 = Patient Health Questionnaire 9; SSQ = Social Support Questionnaire; TF-CBT = trauma-focused cognitive behavioral therapy; UYR = unaccompanied young refugee; WHOQOL-BREF = World Health Organization Quality of Life, brief version. *Subsample of *n* = 100

### Interventions

Before randomization, the first step in all participating CYWS facilities will be a systematic screening of psychopathology, psychosocial difficulties, and indication for treatment (PTSS as measured with the questionnaire CATS-2 as the primary outcome (see the “Measures” section)). The MHCs will undergo training in trauma-informed assessment (screening) and will learn how the written report is to be interpreted and how they can derive the individual indication for prevention or psychotherapy in each of their UYRs (indication).

#### BETTER CARE arm

The stepped-care approach BETTER CARE includes the first step as described above (screening and indication). The second step refers to subclinical cases (CATS-2 score < 25). They will be allocated to the preventive group intervention “Mein Weg.” Participants above the clinical cut-off (≥ 25) will be referred to TF-CBT (step 3). UYRs with a CATS-2 score ≥ 25 who refuse to participate in TF-CBT or who have to wait more than 3 months for TF-CBT treatment will be invited to participate in “Mein Weg” (see Fig. 1).

##### Trauma-focused preventive group intervention “Mein Weg”

The manualized intervention can be delivered by trained non-specialist social workers. It empowers young refugees to cope with their traumatic experiences and stress-related symptoms. The rationale of this intervention is derived from the framework of exposure-based and cognitive interventions for trauma-exposed minors. It aims to empower the social workers in the CYWS programs to gain a deeper understanding of the UYRs’ individual (trauma) history and cultural background and to provide appropriate support to the young refugees. “Mein Weg” is a group intervention delivered in 6–8 sessions lasting between 90 and 120 min. It comprises psychoeducation to normalize psychological symptoms, teaching of a relaxation technique to reduce hyperarousal symptoms, a trauma narrative to counteract dysfunctional avoidance and unwanted intrusions of traumatic memories, and cognitive restructuring to reduce trauma-related cognitive distortions. The aims here are to foster social support, help participants regain a sense of safety, and anticipation of self-efficacy with future challenges. In addition to the evaluated “Mein Weg” manual [14], the author will add 2–3 sessions on problem-management strategies related to asylum stressors.

*Implementation of “Mein Weg”*. In order to implement “Mein Weg” within BETTER CARE facilities, social workers in the CYWS facilities will attend a 2-day training in trauma, trauma-related disorders, their treatment, and the implementation of “Mein Weg” by the author of the manual (EP) and certified “Mein Weg” trainers. During the implementation of the program, social workers will receive weekly case consultations and complete session checklists as fidelity checks.

##### Trauma-focused cognitive behavioral therapy

TF-CBT is a short-term, evidence-based treatment for children and adolescents with PTSD which can be delivered in 12 to 15 sessions [17]. It has nine components that are subsumed with the acronym PRACTICE: psychoeducation and parenting skills (components 1 and 2), relaxation, affect modulation, cognitive coping, trauma narrative, in vivo exposure, conjoint parent-child sessions, and enhancement of safety and development. We will extend TF-CBT by three sessions (up to 18 sessions) that will focus on relapse prevention and problem management related to asylum stressors. A trusted caregiver is to be involved in up to 50% of the treatment sessions and the treatment is usually provided in double sessions (one session with the child and one with the caregiver).

*Implementation of TF-CBT*. TF-CBT is specifically suited to improving social support. It requires a lower level of language skills than interventions for adults. Furthermore, as it has been studied with participants aged three to 18, the level of language requirements can be modified to suit the individual patient. Hence, limited language skills or the involvement of interpreters are no barriers to receiving TF-CBT within this trial. The TF-CBT training package for therapists consists of online training (enriched with culturally adapted materials, http://tfkvt.ku.de), an instructor-led 2-day workshop on the treatment, and case consultations on ongoing cases via telephone (biweekly), each provided by certified TF-CBT trainers. The specific aspects of working with UYRs taught in the workshop will be integrated into the “regular” TF-CBT components (i.e., working with interpreters, preparation for future stressors). Therapists will complete the Brief Practice Checklist Revised (BPC-R [27]) after each session as a measure of fidelity. A TF-CBT treatment case will be deemed to have been completed if at least 8 sessions, including a trauma narrative, have been completed.

To further support the implementation of and decrease barriers to ESTs for UYRs, we will develop a 1-day training session on translation in trauma-focused treatments for interpreters that will be proposed to all suitable (lay) interpreters in the communities of clusters randomized to BETTER CARE.

#### Usual care+ arm

The control condition will be called usual care+ as it presents the usual care that UYRs receive in the CYWS facilities and mental healthcare system enhanced with screening and indication procedures offered by study participation (see step 1). All mental health care utilization will be documented for each participant at every assessment so as to be able to offer a clear description of usual care+ afterwards (Child and Adolescent Mental Health Service Receipt Inventory [CAMHSRI-DE]; [28], see the “Measures” section).

### Measures

All self-report measures will be available in the following languages: German, English, French, Arabic, Kurdish, Dari, Farsi, Pashto, Somali, and Tigrinya. They will be recorded on a tablet computer or on paper by the participant. The respective caregiver will respond to the proxy-report measures in German.

#### Primary outcome

The CATS-2 [26] at the 12-month follow-up is the primary outcome. The first part consists of an event checklist with 15 items to be answered yes/no. The second part consists of 20 items corresponding directly to PTSD criteria according to the Diagnostic and Statistical Manual of Mental Disorders 5 (DSM-5 [29]) They measure the severity of PTSS employing a 4-point scale ranging from 0 (never) to 3 (almost always). To evaluate psychosocial functioning, five dichotomous items (yes/no) investigate whether the rated PTSS interfere with key areas of functioning. Good internal consistency (*α* = 0.75–0.93) has been confirmed in the initial validation [26] and in an RCT with UYRs (*α* = 0.75) [12]. At present, the CATS is accessible in several languages and has been successfully used in previous studies with UYRs [2, 19]. For the current study, a slightly adapted version (CATS-2) will be used to cover ICD-11 PTSD and complex PTSD criteria in addition.

#### Secondary outcomes

All secondary outcomes will be evaluated at the 12-month follow-up. The Patient Health Questionnaire (PHQ-9) [30] comprises 9 items that reflect the criteria for the diagnosis of depressive disorders according to DSM-IV. It showed good reliability (*α* = 0.86–0.89) and has been validated in many contexts and languages [30, 31].

The Generalized Anxiety Disorder Assessment (GAD-7) [32] comprising 7 items assesses symptoms of anxiety according to DSM-IV and has been validated (*α* = 0.92) in many contexts and languages [31].

The World Health Organization Quality of Life-BREF (WHOQOL-BREF [33]) comprises 26 items measuring 4 key areas (physical health, psychological health, social relationships, and environment) over the previous 4 weeks [33]. The short version has been validated in many languages. The Cronbach’s *α* tested in international samples was 0.68–0.82 [34].

#### Exploratory outcomes

The primary and secondary outcomes will be analyzed in an exploratory manner at the 6-month follow-up.

The Alcohol Use Disorders Identification Test (AUDIT) is a 10-item questionnaire used to assess recent excessive drinking and is in conformity with ICD-10 definitions [35]. It is a well-validated (α = 0.80–0.94) [36] measure of risk across gender, age, and cultures.

The Cannabis Use Disorder Identification Test, Revised (CUDIT-R) is an 8-item questionnaire used to assess cannabis use disorder severity [37]. The CUDIT-R has been validated (*α* = 0.91) as both a screening test and a rating scale for cannabis use disorder severity [37].

The EQ-5D-3L [38] is a two-part instrument for the definition and the valuation of health states as the basis for the estimation of quality-adjusted life years (QALYs). It consists of a descriptive part and a visual analog scale similar to a thermometer [39]. At present, the EQ-5D-3L is available in more than 180 languages including all those expected to be relevant for the project.

